### Effectiveness outcomes

Table 2 outlines the effectiveness outcomes.

**Table 2 Tab2:** Effectiveness outcomes

Primary outcome	Measurement	Baseline	30 days	3 months
Referral efficiency	Medical records		x	
Secondary outcomes				
Safety	Medical records		x	
Proportion of CRP POCT^a^	Management data in CRF^a^ Medical records	x		
Proportion of planned reassessment	Management data in CRF^a^ Medical records	x		
Child anxiety	Dutch version of STAIC^a^		x	x
Parental or child satisfaction	Dutch version of P-MISS^a^		x	
Quality of life	EQ-5D-proxy (≤ 7 years), EQ-5D-Y (8–15 years), EQ-5D-3 L (≥ 16 years)^a^		x	x
Costs	Medical records Adjusted iPCQ^a^ and iMCQ^a^		x	x
Other (descriptive) outcomes				
(Adverse) health outcomes	Medical records			x

^a^Abbreviations defined below

*CRP* C-reactive protein, *POCT* point-of-care testing, *CRF* case report form, *STAIC* State-Trait Anxiety Inventory for Children, *P-MISS* Parental Medical Interview Satisfaction Scale, *EQ-5D* EuroQol 5D, *iPCQ* iMTA (Institute for Medical Technology Assessment) Productivity Cost Questionnaire, *iMCQ* iMTA Medical Consumption Questionnaire

#### Primary outcome

The primary outcome is referral efficiency, defined as the proportion of non-referrals in children without appendicitis during 30 days follow-up (Table 3). The diagnosis of appendicitis will be based on imaging, intraoperative findings, and/or histopathology as reported by the secondary care specialist. After 30-days of follow-up, the development of appendicitis is considered highly unlikely.

#### Secondary outcomes

#### Safety

Safety is defined as the proportion of children with appendicitis who are referred during the initial GP consultation or planned reassessment (Table 3).

#### Proportion of children with CRP POCT

The proportion of children in whom CRP POCT was performed during the initial GP consultation will be recorded for each randomised group.

#### Proportion of children with planned reassessment

The proportion of children for whom a planned reassessment was performed after the initial GP consultation will be recorded for each randomised group.

#### Child anxiety

Anxiety in children is assessed using the 20-item Dutch version of the State-Trait Anxiety Inventory for Children (STAIC) at 30 days and 3 months follow-up. The Dutch version of the STAIC (Zelfbeoordelingsvragenlijst voor Kinderen (ZBV-K) Versie Nu) measures self-perceived anxiety based on the state-anxiety subscale and is feasible for children ≥ 8 years. The Dutch version of the state-anxiety subscale has demonstrated good validity and reliability in children (Cronbach’s alpha 0.80 or higher) [45].

#### Parental or child satisfaction about baseline consultation

The satisfaction of parents (children 4–15 years) or children (16–18 years) with the GP consultation is assessed at 30 days follow-up using the Dutch version of the Parental Medical Interview Satisfaction Scale (P-MISS). Comprising 26 items, this questionnaire measures satisfaction regarding communication with parent and child, distress relief and adherence intent, rated on a five-point Likert scale (1 = strongly disagree to 5 = strongly agree) [46]. The P-MISS shows good construct validity and internal consistency (Cronbach’s alpha 0.86–0.95) [46, 47].

#### Child’s quality of life

Quality of life will be evaluated at 30 days and 3 months follow-up using the EuroQol 5D 3 L (EQ-5D-3 L), a generic instrument measuring health-related quality of life (HRQOL). The EQ-5D-3 L includes five domains (mobility, self-care, usual activities, pain or discomfort and anxiety or depression) that are each rated on a three-level severity scale (0 = no problems, 1 = some problems, 2 = extreme problems). The EQ-Visual Analogue Scale records the child’s overall health status with scores ranging from 0 to 100. Parents will complete the EQ-5D-3 L proxy for children aged ≤ 7 years. Children aged 8–15 years will complete the EQ-5D-youth (EQ-5D-Y) and children ≥ 16 years will complete the EQ-5D-3 L. The EQ-5D-Y is highly feasible for assessing HRQOL in children and adolescents with different health conditions [48–51]. Additionally, it has good convergent validity and fair to moderate test-retest reliability (test-retest agreement 70–99%) [49, 51].

#### Costs

Medical and societal costs will be assessed using adapted versions of the iMTA Productivity Cost Questionnaire (iPCQ) and the iMTA Medical Consumption Questionnaire (iMCQ), completed at 30 days and 3 months follow-up. Parents (for children ≤ 15 years) or parents and child (≥ 16 years) will report healthcare use, out-of-pocket expenses, and productivity losses (absence from work). Additionally, researchers will extract information regarding healthcare consumption from children’s medical records (e.g. CRP POCT, GP visits, referrals, hospital admissions, operative and non-operative management in hospital, including antibiotic therapy). All standard-of-care, including all types of healthcare usage, is included in the cost-effectiveness analysis. Medical equipment costs for CRP POCT will be calculated according to the Dutch costing manual, including depreciation, interest, and maintenance costs. Annualized equipment costs will be allocated per procedure based on the expected annual number of measurements on the machine.

The units measured will be monetised according to guidelines of the National Healthcare Institute of the Netherlands [52].

**Table 3 Tab3:** Definitions of safety and efficiency

	Appendicitis +	Appendicitis -
Referred ^a^	a	b
Not referred	c	d

Definitions: Safety (sensitivity) = a / (a + c). Efficiency (specificity) = d / (b + d). The sample size calculation is based on the denominator of the efficiency outcome (b + d)

^a^ Referred at the initial GP consultation for acute abdominal pain or at planned reassessment

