**Methods:**

We will conduct a pragmatic, hybrid type 1 effectiveness-implementation, cluster randomised controlled trial in Dutch general practice. Children aged 4–18 years with acute (≤ 7 days) abdominal pain will be included. GP practices will be randomly allocated to either: (i) use of the diagnostic strategy for appendicitis, or (ii) usual care. In the intervention group, children are stratified into low, medium, or high risk for appendicitis based on a seven-item prediction rule including symptoms and signs. Management advice is tailored to appendicitis risk: safety netting for low-risk, immediate referral for high-risk, or CRP POCT for medium-risk (CRP < 10 mg/L: safety netting; CRP 10–50 mg/L: reassessment or immediate referral (based on GPs’ clinical judgement and parent/child preference); CRP ≥ 50 mg/L: immediate referral). The primary outcome is referral efficiency (proportion of non-referrals amongst patients with no appendicitis during 30 days follow-up). Secondary outcomes include safety, proportion of children with CRP POCT, proportion of children with planned reassessment, child anxiety, patient satisfaction, quality of life, and costs. A parallel process evaluation will assess implementation outcomes, including the reach, adoption, implementation, and maintenance of the diagnostic strategy. We aim to include 566 children without appendicitis to determine an improvement of efficiency from 88% to 95%.

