### Intervention: diagnostic strategy for appendicitis

GPs in the intervention group use a diagnostic strategy for appendicitis that integrates an externally validated seven-item prediction rule with CRP POCT and risk-based management advice. The prediction rule consists of routinely available signs and symptoms, each assigned a point score (Table 1).

**Table 1 Tab1:** Clinical prediction rule for acute appendicitis

Predictor	Point score
Male sex	2
Nausea/vomiting	2
Pain duration < 24 h	1
Pain duration 24–48 h	2
Elevated temperature ≥ 37.3˚ C	1
Abnormal bowel sounds (absent, tinkling or high-pitched)	1
Right lower quadrant tenderness	5
Peritoneal irritation (abdominal rigidity, guarding, rebound tenderness and/or pain with jarring movements)	4

Based on the total score of the prediction rule, children are stratified into three risk groups: low (0–7 points), medium (8–13 points) and high risk (≥ 14 points) for appendicitis. A sensitivity and specificity for appendicitis of ≥ 95% correspond with the lower (7 points) and upper (14 points) cut-offs, respectively [20]. Management advice is tailored to appendicitis risk (Fig. 1): safety netting is advised for low-risk children, while immediate referral is recommended for those at high-risk. For children in the medium-risk group, GPs are instructed to perform CRP POCT. Based on the CRP value, the strategy recommends either safety netting (CRP < 10 mg/L), reassessment or immediate referral depending on the GP’s clinical judgment and parent/child preference (CRP 10–50 mg/L), or immediate referral (CRP ≥ 50 mg/L). The reassessment is considered a continuation of the initial consultation and includes a repeat clinical assessment and, if indicated, CRP POCT, and should take place later the same day or, if not feasible, the following morning. Cut-offs for CRP were derived from previous primary care research, where CRP ≥ 10 mg/L showed 0.87 (95% CI 0.77–0.94) sensitivity for appendicitis, increasing to 1.00 (95% CI 0.89-1.00) after 48 h, and CRP ≥ 50 mg/L demonstrated 0.94 (95% CI 0.93–0.96) specificity [21].

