Still, our study has some limitations. First, although the cluster design reduces potential contamination between GPs [74, 75], it can introduce selection bias if GPs in the intervention arm include children with different characteristics (e.g. more severe symptoms) than those in the control group [76]. To address this, missed eligible children are identified retrospectively via GP registries, and their characteristics compared with those of included children for both groups, with adjusted analyses conducted if baseline differences are observed. Second, GPs and patients are not blinded, which may lead to bias. However, we consider this bias to be limited, as pragmatic trials assess overall effects on the care pathway rather than isolated intervention effects [27]. Third, children presenting at out-of-hours primary care service are not included because of logistical constraints related to the inclusion of GPs and children at these services, particularly the training of an unfeasibly large number of GPs and the reviewing of medical records at numerous individual practices within the service’s catchment area. This may limit generalizability of findings to out-of-hours settings due to potential differences in urgency and severity of appendicitis.

In summary, this study will evaluate whether a diagnostic strategy for appendicitis in children presenting to their GP with acute abdominal pain can reduce referrals to secondary care without increasing delayed diagnoses, compared to usual care. If our hypothesis is confirmed, the findings may support its adoption in routine practice, ultimately contributing to more efficient care and better outcomes for these children.

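### Efficiency counts a referral only at the initial consultation or planned reassessment, so on its own it cannot show that the strategy reduces referrals

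*Protocol article*

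**What the plan says.** All references are to the protocol article.

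- **Primary outcome** describes referral efficiency as "defined as the proportion of non-referrals in children without appendicitis during 30 days follow-up" and points to Table 3. The Methods part of the Abstract words it as the "proportion of non-referrals amongst patients with no appendicitis during 30 days follow-up".
- **Table 3** (printed under Costs) sets efficiency = d/(b + d), where b is referred and d is not referred among children without appendicitis. Footnote a defines the referred row: "Referred at the initial GP consultation for acute abdominal pain or at planned reassessment".
- **Safety** uses the same row. It is the proportion of children with appendicitis "who are referred during the initial GP consultation or planned reassessment", that is a/(a + c).
- **Intervention: diagnostic strategy for appendicitis** says of the reassessment: "The reassessment is considered a continuation of the initial consultation". It adds that the reassessment "should take place later the same day or, if not feasible, the following morning".
- **Control: usual care** says that GPs in doubt are advised to plan a reassessment. It states no time window.
- **Randomisation, allocation and blinding** says that GPs, patients and outcome assessors are not blinded. Only the data analysts are.
- **Discussion** closes by asking whether the strategy "can reduce referrals to secondary care without increasing delayed diagnoses, compared to usual care". The Abstract's hypothesis is equally general.

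**The concern.** The outcome and the claim are not about the same quantity. The strategy advises safety netting for low-risk children and for medium-risk children with a CRP below 10 mg/L, so an unplanned return followed by referral is a foreseeable path. Such a referral falls outside footnote a and is scored as a success. A positive primary result would show fewer referrals at the index decision. It would not show how many of those referrals were avoided and how many came later.

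The second issue is the label. Whether a visit was a *planned* reassessment decides b versus d for efficiency and a versus c for safety. Unblinded clinicians generate the label, and the article gives it a time frame in one arm only. A control reassessment arranged some days ahead could put a referral in b, while an intervention child first referred at an unplanned visit on that same day would go to d.

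The efficiency measure is also the effect parameter in the cost-effectiveness ratio, while costs take in all healthcare use. A late referral of a child without appendicitis would add cost and still count as an effect.

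**Working it through.** **1. Where a child without appendicitis is counted under footnote a**

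| Path | Cell | Scored as |
|---|---|---|
| Referred at initial consultation | b | not efficient |
| Referred at planned reassessment | b | not efficient |
| Sent home, first referred at an unplanned return | d | efficient |
| Never referred | d | efficient |

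Only the third path separates the index measure from a count of all referrals in the episode.

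**2. The plan's own figure.** Inputs from Sample size considerations: 88% versus 95%, two-sided 5%, 80% power, cluster size 3, intraclass correlation 0.01, 10% loss.

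- Design effect: 1 + (3 − 1) × 0.01 = 1.02.
- Two proportions, pooled variance under the null: [1.960 × √(2 × 0.915 × 0.085) + 0.842 × √(0.88 × 0.12 + 0.95 × 0.05)]² / 0.07² = 248 per arm.
- 248 × 1.02 = 253 per arm, 506 in all, against 510 stated. 510/0.9 = 566.7, against 566 stated.
- Power at 255 per arm (255/1.02 = 250 effective): 80.3%.

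The sample size reproduces. The point concerns the definition and not the arithmetic.

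**3. Counting later referrals.** Let u be the share of children scored as not referred who are referred later at an unplanned contact. Efficiency over the whole episode = index efficiency × (1 − u). The documents give no value for u, so every rate below is an assumption. Power is for 250 effective children per arm.

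| u intervention | u control | Intervention | Control | Difference (points) | Power |
|---|---|---|---|---|---|
| 0% | 0% | 95.00% | 88.00% | 7.0 | 80% |
| 1% | 1% | 94.05% | 87.12% | 6.9 | 76% |
| 2% | 2% | 93.10% | 86.24% | 6.9 | 71% |
| 3% | 3% | 92.15% | 85.36% | 6.8 | 67% |
| 3% | 1% | 92.15% | 87.12% | 5.0 | 45% |
| 5% | 1% | 90.25% | 87.12% | 3.1 | 20% |
| 1% | 2% | 94.05% | 86.24% | 7.8 | 84% |

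With u = 0 in controls, the whole 7 points would vanish at u = 1 − 0.88/0.95 = 7.4% in the intervention arm.

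**4. Limiting case.** Suppose that 12% of children without appendicitis are referred in both arms over the episode, and that the strategy only moves a share s of its referrals to unplanned visits. Apparent intervention efficiency is 1 − 0.12 × (1 − s), against 88% in controls.

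- s = 20%: 90.4%, with a 14% chance of a significant result favouring the intervention.
- s = 50%: 94.0%, with a 65% chance.
- s = 0: 2.5%.

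This shows what the definition allows. It is not evidence that it happens.

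**The case against.** The case for leaving the outcome alone is strong in several respects.

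- **It is a coherent choice.** Table 3 labels the two outcomes sensitivity and specificity, and one index decision is being scored. This stands.
- **The strategy's own deferral route is captured.** A referral at the reassessment offered for CRP 10–50 mg/L goes to cell b. Only unplanned returns escape. This stands.
- **Widening the referred row would damage safety.** The row serves both outcomes. If it took in any contact, a child with appendicitis who was sent home and referred at an unplanned return would move from c to a, and missed cases would look safe. This stands, and it rules out simply redefining *referred*.
- **Silence is not proof.** The case report form and extraction form (Supplementary 6 and 7) are not shown and may define planned reassessment for both arms. A supportive analysis may sit in an analysis plan that is not shown, so its absence from the article is not an error. This stands for the missing detail. It does not alter the gap between the outcome as defined and the claim as worded.
- **Later referrals are not ignored.** They are extracted from records and enter the costs. True, but no efficiency result described in the article uses them.

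**Conclusion.** The point holds in a limited form. From footnote a and d/(b + d), the primary outcome measures referral at the index consultation or planned reassessment. It does not by itself support a general statement that referrals fall. The difference in how reassessment is described for the two arms leaves room for different classification of an unblinded label, in efficiency and in safety. Safety is secondary and is acknowledged in the Discussion to be underpowered.

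Two stronger readings are tempting and should not be drawn.

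- A reader might infer that Primary outcome and the 30-day column of Table 2 contradict Table 3. They do not. The Abstract attaches the 30 days to the absence of appendicitis. Primary outcome justifies the period by saying that later appendicitis is highly unlikely, and Table 2 gives safety the same column although safety is explicitly limited to the index decision. The sentence in Primary outcome is loosely ordered, no more.
- A reader might infer that the trial is biased towards the intervention. The documents give no unplanned-referral rate. The loss from 7.0 to 5.0 points, with about 45% power, rests entirely on the assumed 3% versus 1%. Equal rates barely move the difference, and higher rates in controls increase it.

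**What to change.** 1. Keep the index-decision definition for the primary outcome and for safety. Enrolment has run since March 2025, and a new primary definition would also require rechecking the 88% and 95% assumptions.
2. Reword the Primary outcome sentence so that the 30 days plainly govern disease status, and cite footnote a there.
3. Code *planned reassessment* for analysis by one written rule applied identically in both arms. This concerns outcome classification only and implies no change to care in either arm.
4. Prespecify a key supportive analysis, in children without appendicitis only: any referral for the episode, from any source, within 30 days. State beforehand what agreement with the primary result means. The analysis may have less power than the primary one (71% with 2% later referral in both arms), so the estimate and its interval should carry the judgement.
5. For children with appendicitis, report time from first consultation to referral alongside safety.
6. Conclude that the strategy reduces referrals only if the 30-day analysis agrees. Otherwise limit the conclusion to referral at the index consultation or planned reassessment.

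The cost is a wording change, some extra analysis of medical-record data already being collected, and possibly a narrower conclusion. It should be settled before allocation is revealed to the analysts.

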### Control: usual care

GPs in the control group provide usual care at their own discretion. They are advised, but not obliged, to follow the NHG guideline ‘Abdominal pain in children’, which lacks specific referral criteria for appendicitis. The guideline advises suspicion of appendicitis in children with right lower quadrant pain, tenderness, and fever, and referral in case of peritonitis signs or abnormal bowel sounds. When in doubt, GPs are advised to plan a reassessment. CRP testing is not recommended due to lack of evidence. During a site initiation visit prior to the start of the study, the researchers present a summary of the NHG guideline to GPs. No additional education and/or materials are provided.

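### Efficiency as defined in Table 3 measures referral at the index episode only, so it cannot tell avoided from postponed referrals, and no listed outcome compares total referrals over 30 days

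*Protocol article*

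**What the plan says.** The Primary outcome section introduces efficiency as "referral efficiency, defined as the proportion of non-referrals in children without appendicitis during 30 days follow-up (Table 3"), and Table 2 places it in the 30-day column. Table 3 gives the formula "Efficiency (specificity) = d / (b + d"), and its footnote restricts the referred row to children "Referred at the initial GP consultation for acute abdominal pain or at planned reassessment". The intervention section treats the planned reassessment as part of the initial consultation, to be held the same day or the next morning.

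Safety uses the same referral window, in children with appendicitis.

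Referrals also appear among the items taken from medical records for costing ("CRP POCT, GP visits, referrals, hospital admissions"). The cost-effectiveness analysis uses efficiency as its effect measure.

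The abstract's hypothesis is that the strategy will reduce referrals. The Discussion asks whether the strategy "can reduce referrals to secondary care without increasing delayed diagnoses, compared to usual care". Neither statement is limited to the index episode.

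**The concern.** The 30 days in the outcome definition can be attached to two different things: the period in which referrals are counted, or the period in which appendicitis status is settled. Table 3 allows only the second. A child without appendicitis who goes home, comes back unplanned on day 3 and is then referred falls in cell d and counts as a success.

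Nothing else in the outcome list picks this up. Safety registers a late referral only in children with appendicitis. The cost analysis counts the later referral as resource use, but its effect measure still scores that child as efficiently managed.

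What is at stake is the meaning of a positive result. It would show that fewer children without appendicitis are referred at the first consultation or planned reassessment. It would not by itself show that fewer of them end up in secondary care, which is how the hypothesis and the closing summary would naturally be read.

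**Working it through.** **Step 1. What is counted.** Reading the Primary outcome section, Table 3 and the intervention section together, for a child without appendicitis:

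| Course within 30 days | Cell in Table 3 | Scored as |
|---|---|---|
| Referred at initial consultation | b | failure |
| Referred at planned reassessment | b | failure |
| First referred at a later unplanned contact | d | success |
| Never referred | d | success |

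The last two rows cannot be told apart in the primary outcome. The rule is the same in both arms.

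**Step 2. Reproduce the plan's figure.** Inputs from Sample size considerations: efficiency 88% vs 95%, 80% power, two-sided 5%, cluster size 3, intraclass correlation 0.01.

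- Two-proportion z test: 248 per arm.
- Design effect: 1 + (3 − 1) × 0.01 = 1.02.
- 248 × 1.02 = 253 per arm, against 255 stated.
- 510 / 0.9 = 567, against 566 stated.
- Power with 255 / 1.02 = 250 effective children per arm: 80.3%.

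The sample size stands. The point is not an arithmetic error.

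**Step 3. Any referral within 30 days.** The article gives no rate of later unplanned referral, so the rates here are assumptions. Index referral is 1 − 0.88 = 12% in control and 1 − 0.95 = 5% in the intervention arm. Then

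any referral = index + (1 − index) × later rate among children not referred at the index episode.

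Control, assumed later rate 2%: 0.12 + 0.88 × 0.02 = 13.8%.

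| Assumed later rate, intervention arm | Any referral, intervention arm | Difference from control (points) | Difference in primary outcome (points) | Power for any referral |
|---|---|---|---|---|
| 2% | 0.05 + 0.95 × 0.02 = 6.9% | 6.9 | 7 | 71% |
| 4% | 0.05 + 0.95 × 0.04 = 8.8% | 5.0 | 7 | 42% |
| 6% | 0.05 + 0.95 × 0.06 = 10.7% | 3.1 | 7 | 18% |
| 8% | 0.05 + 0.95 × 0.08 = 12.6% | 1.2 | 7 | 7% |

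Power uses the same z test with 255 per arm and design effect 1.02.

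With 2% in control, the net difference disappears when the later rate in the intervention arm reaches (0.1376 − 0.05) / 0.95 = 9.2%.

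**Step 4. What drives the result.** With equal later rates the index difference carries over almost unchanged. The two outcomes part only if later unplanned referral is more frequent in one arm. The article has no figure on which to judge that.

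**The case against.** The strongest defence is that the definition is deliberate and explicit. The outcome text points to Table 3. The abstract attaches the 30 days to the absence of appendicitis, and the Primary outcome section explains that appendicitis is highly unlikely to develop after that time. The anticipated 95% is built from test specificities of 97% and 94%, which fits an index-decision outcome, and safety uses the same window. Later referrals are not ignored either, since they enter the costs at 30 days and 3 months. All of this stands. It is why the primary outcome should be kept.

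A reader might go further and infer that the comparison is tilted towards the intervention. Usual care advises planning a return visit ("When in doubt, GPs are advised to plan a reassessment"), where a referral counts. In the strategy, "safety netting is advised for low-risk children, while immediate referral is recommended for those at high-risk", and a referral at an unplanned return after safety netting does not count. The documents do not support that inference. One rule applies to both arms. The strategy has its own planned reassessment, for medium-risk children with CRP 10–50 mg/L, and a referral there counts against it. Control children sent home without a planned reassessment escape the count in the same way. The proportion with a planned reassessment is itself a secondary outcome reported by arm. A tilt is possible but not shown.

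A reader might also infer that a reduction in referrals is not tested at all. That is too strong. Reduction at the index episode is tested, and only a net reduction is not. The extreme case, in which all 7 points are merely postponed and the trial still has 80% power to declare superiority, is a bound and not a forecast.

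The defence does not answer the remaining point. Costs pool many items and do not compare referral counts, and the article's stated aim is not limited to the index episode.

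**Conclusion.** The point holds as a gap between the outcome and the conclusion drawn from it, and should be fixed. Efficiency is a valid index-episode measure, but it cannot distinguish avoided from postponed referrals. No listed outcome compares total referrals by arm, and the wording around 30 days invites the wrong reading.

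The size is unknown. Under the assumed rates above, the net difference ranges from 6.9 points (equal later referral of 2%) down to 1.2 points (2% in control, 8% in the intervention arm), against a constant 7 points on the primary outcome. This rests on the planned 12% and 5% index referral and on later rates that do not come from the article. The direction of any distortion is not established.

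**What to change.** 1. In the Primary outcome section and Table 2, state that efficiency refers to referral at the initial consultation or planned reassessment, and that the 30 days serve to establish whether the child had appendicitis.
2. Pre-specify a supporting secondary outcome in children without appendicitis: any referral to, or attendance at, secondary care for abdominal pain within 30 days. Analyse it with the same logistic mixed model (allocation and practice size as fixed effects, practice as random effect) and report the estimate with its 95% confidence interval.
3. Word the conclusion as a reduction in referral at the index episode, unless the estimate and interval of that supporting outcome support a net reduction.

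The primary outcome, sample size and model stay as they are. The data come from the record extraction already planned for costs, so no extra children or visits are needed. The cost is one more outcome with lower power than the primary (71% even under equal later referral of 2%), and possibly a narrower conclusion. Inclusion is expected to run until January 2028, so the change can be made before the analysis.
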